**1. Aims of the project**

The primary aim of this study is to increase timely diagnosis of dementia through an evidence-based intervention promoting memory service access. We will test in a randomised controlled trial if this intervention increases the number of people with undiagnosed dementia presenting with memory related problems to their GP; the number of patients GPs refer appropriately to memory services; and if this referral is at an earlier stage. We are currently collaborating with the Alzheimer’s Society and their reference groups (including the GP reference group) to redesign the evidence-based CHOICE leaflet1 to ensure usability, acceptability and relevance, and to develop a personal letter from GPs to the “at risk” population to accompany the leaflet.

Research questions

Does sending a leaflet1 on how to overcome barriers to accessing help for dementia to people aged over 70 registered in a general practice, with an accompanying personal letter from the GP, lead to people with dementia presenting earlier to specialist dementia services compared with usual care over 12 months, and if so is it at low cost? We will test the hypotheses that over 12 months people receiving the intervention will present earlier (mean of 3 points higher on MMSE score)2 than those not receiving it and that the costs of the intervention are small.

Primary objective

To enable people with dementia to receive an earlier diagnosis

Secondary objectives

1. To increase the number of people with dementia receiving diagnoses
2. To increase the numbers of people with memory problems presenting to GPs.
3. To calculate the cost-effectiveness of the intervention considering the cost of implementing the CHOICE intervention and the numbers of appropriate and inappropriate referrals to memory services.

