**8. Data collection**

All data will be anonymised and collected for intervention and control practices. Consent will be through cluster guardians32, who will provide consent for collection of this data33.

1. Sociodemographic data about the person with suspected dementia will include gender, age, ethnic status according to census, marital status, education, living situation and location. We will record GP characteristics and practice size.
2. **The primary outcome** is the cognitive score as measured by the Mini Mental State Examination (MMSE)34 of people referred to memory services in the intervention and control groups who receive a diagnosis of dementia. The minimum clinically important difference in MMSE score is three points2 and is the most widely used standard test of cognitive function34. We will collate the baseline MMSE score from the new patients’ presenting to memory clinic (i.e. MMSE scores of new presentations) at 3, 6 and 12 months after sending the letters. We are not collecting follow-up MMSEs. There is a maximum score of 30, with scores of 0-10=severe, 11-20=moderate, and 21-24=mild dementia35.
3. **Secondary outcomes**

- Number of people presenting with a possible diagnosis of dementia will be collected from GPs practices using MiQUEST36 (a Department of Health computer system allowing anonymised data extraction from GP practices). [name] is an expert in using this and is one of the project team. We will collect the number of people presenting to their GP who are and who are not referred on to memory services.
- Numbers of patients referred to memory services from participating intervention and control practices
- The number of memory services appointments offered and people attending for diagnostic assessment,
- The number of people referred who do not have dementia or mild cognitive impairment
- Costs of implementing the intervention, including the costs associated with the CHOICE leaflet (printing, and distribution), GP visits to discuss possible diagnoses of dementia, and use of memory services, and the cost of assessing those with and without dementia
- We will systematically ask clinicians about any inappropriate presentations and patient distress and record these as adverse events.

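### Restricting the primary MMSE to people who receive a dementia diagnosis removes those who come early enough to be labelled MCI, so the plan is expected to understate earlier presentation

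*Protocol*

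**What the plan says.** Section 1 asks whether the intervention brings people to specialist services sooner, "and if this referral is at an earlier stage". It equates sooner with a higher score: "people receiving the intervention will present earlier (mean of 3 points higher on MMSE score".

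Section 8 defines the primary outcome as the MMSE of people referred to memory services "in the intervention and control groups who receive a diagnosis of dementia". It then describes the collection more widely, as baseline scores of new memory-clinic patients ("i.e. MMSE scores of new presentations) at 3, 6 and 12 months after sending the letters"), and adds: "We are not collecting follow-up MMSEs".

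MCI is named in one secondary outcome only: "The number of people referred who do not have dementia or mild cognitive impairment". The cost item separates "the cost of assessing those with and without dementia". No listed outcome counts people with MCI or uses their scores.

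Section 10 compares mean MMSE between arms on complete cases. Multiple imputation and inverse probability weighting are planned as sensitivity analyses for missing data.

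**The concern.** The primary comparison is conditioned on a diagnosis made after randomisation, and its probability depends on how early a person comes. The letter and leaflet are meant to change exactly that.

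Take a person who, without the letter, would be diagnosed with dementia near the end of the 12 months. In the control arm that person's MMSE enters the mean. In the intervention arm the same person may come sooner, score higher, be labelled MCI and contribute nothing. No later MMSE is collected, so the person does not return to the data. Those removed sit at the top of the score distribution, and they are among the people the intervention helped most on the trial's own definition.

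The planned missing-data methods do not touch this, because these scores are not missing; they are excluded by definition. A trial analysed exactly as written could report a small or null difference when presentation had in fact moved earlier.

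**Working it through.** **Inputs.** From Section 9: mean 19.5 and SD 6.1 in an audit of people with dementia, a difference of 3 points, alpha 5% (sidedness not stated), power 90%, ICC 0.03, 11 referrals per practice. The share labelled MCI and the MMSE at which that label is given are not in the protocol; every value used for them below is an assumption.

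**Reproducing the plan's figure.** n per arm = 2 × ((z_alpha + z_power) × 6.1 / 3)².
- One-sided 5%: 2 × ((1.645 + 1.282) × 6.1/3)² = 70.8, so 71, which matches.
- Two-sided 5%: 86.9, so 87, which does not match.
- Design effect 1 + (11 − 1) × 0.03 = 1.3; 71 × 1.3 = 92.3, so 93, which matches.

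Sidedness is a separate matter, so both versions are shown.

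**Power without relabelling.** SE = 6.1 × √(2 × 1.3/93) = 1.02. 3/1.02 = 2.94. Power = Φ(2.94 − 1.645) = 90% one-sided and Φ(2.94 − 1.960) = 84% two-sided.

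**Effect of relabelling.** Leave the control arm at 19.5, since the audit is already dementia-only. Shift everyone in the intervention arm by 3, to a mean of 22.5. Remove only those who would have been below the cut and are now at or above it. With q the share removed and M their mean score, the mean of those kept is (22.5 − qM)/(1 − q). Whole-number cuts are placed half a point lower (25+ means above 24.5).

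| Cut for MCI | q | M | Mean kept | Difference seen | SD kept |
|---|---|---|---|---|---|
| 25+ | 16.5% | 25.9 | 21.8 | 2.3 | 6.4 |
| 27+ | 13.0% | 27.9 | 21.7 | 2.2 | 6.1 |
| 29+ | 9.3% | 29.9 | 21.8 | 2.2 | 5.9 |

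For 27+: (22.5 − 0.130 × 27.9)/0.870 = 21.7.

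The Normal curve runs past 30. A simulation with control scores drawn within 0-30 (mean 18.9, SD 5.5), shifted scores capped at 30 and cuts of 24 to 27 leaves 2.0 to 2.1 points of a true gain of 2.9. Together the two versions give 2.0 to 2.3.

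**Power after relabelling** (Normal version, 93 per arm before removal, design effect 1.3). SE = √(1.3 × (6.1²/93 + SD_kept²/(93(1 − q)))). For 27+ this is 1.06, and 2.19/1.06 = 2.07, so power is 66% one-sided and 54% two-sided. For 25+ it is 68% and 56%; for 29+ it is 71% and 59%.

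**Can the sign reverse?** Treat q and M as free, with a true gain of 3. With M = 27 the difference seen is 2.5 at q = 10%, 1.9 at 20%, 1.1 at 30% and 0.0 at 40%. With M = 28 and q = 40% it is −0.7. If only people who would have presented at 21 or more gain 3 points (true mean gain 1.0), relabelling 30% of them leaves +0.1, 40% gives −0.25 and 50% gives −0.65. A uniform shift with one cut attenuated the difference but did not reverse it.

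**The case against.** **The population matches the question.** The primary objective concerns people with dementia, the sample size counts people with dementia, and MCI is not dementia. That stands as a reason to keep the dementia-only primary. It does not remove the bias, because who counts as having dementia at first assessment depends on timing.

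**An extra analysis can be left to the analysis plan.** In part. But the outcome population and the data to be extracted are fixed in Section 8, and Section 12 ties collection to that section. If diagnostic class is not kept for people with MCI, no later plan can recover it.

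**The data may already be there.** This largely stands. Section 8 collates MMSE from new presentations generally, and counting referrals with neither condition requires the services to separate MCI. It makes the remedy cheap; no listed outcome or analysis uses these scores.

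**Adding MCI can bias the other way.** This stands. A mailed leaflet may bring in people with MCI who would never progress, which raises the intervention mean without any earlier dementia diagnosis.

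Three stronger readings are tempting and are not supported:
- A reader might infer that the intervention arm's mean is likely to fall. The calculations show that this needs gains concentrated in the mildest presenters, with more than about a third of them relabelled, or about 40% of all presenters relabelled with a mean above 27. Nothing in the protocol points to either.
- A reader might infer that Section 8 treats MCI inconsistently. It does not. An MCI referral can be acceptable, be costed as without dementia, and be outside a dementia outcome; these answer different questions.
- A reader might cut both arms at the same score. That truncates an audit distribution that is already dementia-only and contradicts its mean of 19.5.

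**Conclusion.** The point holds as one of attenuation. The primary outcome is restricted by a post-randomisation diagnosis that the intervention can shift, and nothing in the protocol's analysis section addresses it. Under a uniform 3-point gain, with removal only of people crossing an assumed cut of 25+ to 29+, roughly a quarter to a third of the effect is lost (2.0 to 2.3 points remain). Power at 93 per arm drops from 90% to about 66-71% one-sided, or from 84% to about 54-59% two-sided.

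The direction of this mechanism follows from the text. The size does not, since the protocol gives neither an MCI rate nor a diagnostic cut and a sharp cut is a simplification. Reversal is a possibility under special conditions, not the expected result.

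**What to change.** Keep the dementia-only primary outcome and add to the protocol:

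1. For every new presentation whose MMSE is already collated, record one of three classes: dementia, MCI or neither.
2. Report the number with MCI in each arm per eligible registered person.
3. Pre-specify a sensitivity analysis of first MMSE in people with dementia or MCI, using the same clustered model as the primary.
4. State that a null dementia-only result is not by itself evidence of no earlier presentation.
5. State that the dementia-plus-MCI analysis can favour the intervention, because some MCI never progresses, so it is a sensitivity analysis to be read beside the MCI counts.

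The cost is a few sentences of protocol text and, at most, one further field from a memory-service record already in use. The sample size and primary analysis do not change.

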**9. Power calculations and statistical methods to be used**

Sample size

Approximately 14% (1 in 7) of people aged >70 have dementia37. The average GP registered patient population is ≈200038, of whom 260 (13%)39 are ≥70 years old. Thus there is a mean of 36-37 patients with dementia per GP of whom 24 would be unknown. An audit of people with dementia presenting to Islington memory services showed a mean MMSE score =19.5 (standard deviation=6.1). A clinically significant difference between experimental and control arms =3 points in MMSE2. To achieve this would require 71 undiagnosed people with dementia in each group (=5% and power=90%). In Islington last year 420 patients were referred from the 38 practices – a mean of 11/practice. Since families in group practices may receive the intervention letter from one GP then consult and be referred by another, cluster randomisation is appropriate and will be used to allocate GP practices to the intervention or control arms. Consequently, we need to inflate the sample based on a projected intracluster correlation of 0.0340. The required sample size in each arm is then 93. This will equate to 8580 people aged over 70 registered with the GPs. If 11 patients are referred per practice, we require approximately nine practices (clusters) in each trial arm. The primary outcome is routinely collected data; but some patients will become too ill or die, or refuse assessment by the clinics. Estimated level of attrition rate=18% (18% loss to follow up in LASER including deaths- a previous dementia study in the community), and therefore we aim to recruit 11 GP practices in each arm. Randomisation will be computerised and stratified by geographical location. The allocation ratio will be 1:1.

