**10. Analysis**

We will report descriptive sociodemographic and clinical data by randomisation group. We will conduct between group comparisons for categorical and linear data. We will compare the mean MMSE from each group and will use t-tests or Mann-Whitney where appropriate. Statistical modelling will be performed in the form of hierarchical multivariate regression analysis, to account for clustering of patients. Analysis of covariance (ANCOVA) will be used to adjust for baseline differences in outcome variables and multiple linear regression will be used to identify other predictors of MMSE at presentation e.g. gender, age and ethnicity. In the regression analysis we will account for the clustering effect in suitable ways (e.g. random effects models). We plan to perform a primary analysis on complete cases and then develop secondary analyses adjusting for potential missing data using suitable methods (e.g. multiple imputations, and inverse probability weighting). We will apply these as sensitivity analysis and discuss them in conjunction with the main analysis. Missing data is accounted for in the sample size calculations; thus we should be able to observe enough complete cases to preserve the power for the main analysis. For the cost analysis the costs associated with printing and distributing the CHOICE leaflet will be based on market prices. Numbers of GP visits will be taken from MiQUEST29 and numbers of contacts with memory services will be taken from practice records. All contacts will then be costed by applying unit costs from published sources41. We will then calculate and compare the mean cost of delivering the intervention per patient and the use of GP and memory services in each arm.

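### The 71 per arm is an undeclared one-sided 5% figure; read two-sided, the planned 22 practices give about 82–87% power, not 90%

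*Protocol*

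**What the plan says.** Section 9 of the protocol takes the variability of the primary outcome from a local memory-service audit that "showed a mean MMSE score =19.5 (standard deviation=6.1"). It sets the target as "A clinically significant difference between experimental and control arms =3 points in MMSE2" (the final 2 is a reference number). At 5% significance and 90% power it concludes: "To achieve this would require 71 undiagnosed people with dementia in each group".

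The rest of the sample size is built on that figure:
- For practice-level randomisation, "we need to inflate the sample based on a projected intracluster correlation of 0.0340" (an ICC of 0.03, followed by a reference number), with 11 referrals per practice. This leads to "The required sample size in each arm is then 93", or about nine practices per arm.
- Attrition of 18% raises this to 11 practices per arm, 22 in all. On allocation, "The allocation ratio will be 1:1".

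On the test itself, section 10 says: "We will compare the mean MMSE from each group and will use t-tests or Mann-Whitney where appropriate". It adds regression models that allow for clustering. Neither section says whether the 5% is one-sided or two-sided. The hypothesis in section 1 has a direction, that "people receiving the intervention will present earlier (mean of 3 points higher on MMSE score"), but no one-sided test is declared there or elsewhere.

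**The concern.** A significance level of 5% given without qualification, beside t-tests, Mann-Whitney tests and regression, will normally be read as two-sided. The printed 71 does not agree with that reading, since the protocol's own inputs then call for 87. The later targets (93 per arm, nine practices, eleven practices) all start from 71, and section 10 relies on the sample size again when it argues that complete cases will be enough to keep the power of the main analysis.

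The interpretation of a null result is at stake. Readers would take it as coming from a trial with a 10% chance of missing a true 3-point difference. Under two-sided testing that chance is larger. If the test is one-sided, readers need to know that the error rate in the favourable direction is 5%, twice that of a two-sided 5% test.

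**Working it through.** **Inputs (protocol, section 9).** Difference d = 3; SD = 6.1, so SD² = 37.21; significance 5%; power 90%; 1:1 allocation; ICC 0.03; 11 patients per practice; attrition 18%; 11 practices per arm.

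**1. Reproducing the 71.** Per-arm size for two means: n = 2(z_α + z_β)² SD² / d².
- One-sided 5%, 90% power: 2 × (1.645 + 1.2816)² × 37.21 / 9 = 70.8, hence **71**. This matches.
- Two-sided 5%, 90% power: 2 × (1.960 + 1.2816)² × 37.21 / 9 = 86.9, hence **87**. The t-test version gives 87.9, hence 88.
- Two-sided 5% at 80% power gives 64.9 and at 85% gives 74.2, so a lower power does not explain 71.
- A two-sided 90% calculation would give 71 only with an SD of about 5.5, not the audited 6.1.

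**2. Reproducing the 93.** Design effect = 1 + (11 − 1) × 0.03 = 1.3, and 71 × 1.3 = 92.3, hence **93**. This matches and confirms how the chain was built.

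**3. Power at the stated size.** Power = Φ(d / (SD × √(2/n)) − z_α).
- One-sided at n = 71: Φ(2.930 − 1.645) = 90.1%.
- Two-sided at n = 71: Φ(2.930 − 1.960) = 83.4% (82.9% by t-test).
- Two-sided at 93 clustered: 93 / 1.3 = 71.5 effective, giving 83.7%.

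**4. Power of the planned design, two-sided.** Evaluable per arm: 11 practices × 11 patients × 0.82 = 99.2, about 99. Two design effects are reasonable: the protocol's implied 1.3 (11 per practice), or 1 + (9 − 1) × 0.03 = 1.24 (about 9 analysed per practice). The t reference uses 22 − 2 = 20 df, because practices are the randomised units.

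| Design effect | Effective n per arm | Normal reference | t on 20 df |
|---|---|---|---|
| 1.3 | 99 / 1.3 = 76.2 | 86% | 82% |
| 1.24 | 99 / 1.24 = 79.8 | 87% | 84% |

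**5. What two-sided 90% would need on the protocol's own route.** 87 × 1.3 = 113.1, hence about **114** evaluable per arm, against 93. Allowing for 18% attrition: 114 / 0.82 = 139 per arm, and 139 / 11 = 12.6, hence 13 practices per arm.

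**The case against.** The strongest reply is that the protocol never describes a two-sided test. A reader might infer from section 10 that the planned tests are two-sided and that the 90% is therefore simply wrong. The documents do not support that. Section 10 gives no sidedness, and the hypothesis in section 1 is directional. If a one-sided 5% test is intended, 71 gives 90.1% power, 93 and nine practices follow, and the chain is consistent. This objection stands, and the shortfall must be stated conditionally. It does not remove the point, because a directional hypothesis is not a declaration of a one-sided test and no justification for one is given. An effect in the other direction is also conceivable: a letter that brought forward people with long-undiagnosed, more advanced dementia could lower the mean MMSE at presentation.

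A second tempting reading is that the trial as planned has 83% power, and so a 17% chance of missing the target. That figure belongs to 93 evaluable per arm. Rounding up to 11 practices gives about 99, and the two-sided miss rate is then about 13–18%, depending on the design effect and reference distribution. The protocol fixes neither refinement, which is why a range is given.

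Finally, a symbol before the 5% was lost in text extraction, and a word on sidedness could in principle have stood there. A single Greek letter is more likely. If the original does say one-sided, what remains is to justify it.

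**Conclusion.** The point holds in conditional form. That 71 is a one-sided 5% calculation is settled arithmetic: of the one- and two-sided 5% calculations tried on the stated inputs, only one-sided with 90% power gives it. The protocol does not say so. Under the conventional two-sided 5% reading, the stated 90% is not delivered: power is about 83% at 71 effective (93 clustered) per arm, and about 82–87% for the planned 11 practices per arm. That range rests on a 3-point difference, SD 6.1, ICC 0.03, 11 referrals per practice and 18% attrition being right. It spans 86–87% with a normal reference and 82–84% with t on 20 df, for design effects of 1.3 and 1.24. Under a declared one-sided 5% test, the 71, 93 and 90% stand as printed.

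The allocation, endpoint and estimate are unaffected. What needs correcting is a power claim whose basis is not disclosed.

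**What to change.** State the sidedness of the primary test in section 9, and use the same statement for the analysis in section 10.

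- **If two-sided 5%:** replace the 90% with the power that the planned 22 practices deliver (about 82–87%), stating the evaluable number, design effect and reference distribution behind it. Give 87 before clustering and about 114 evaluable per arm after it as the figures that two-sided 90% would need.
- **If one-sided 5%:** say so and justify it, so that 71, 93 and 90% are not taken for two-sided figures.

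Either route is a change of wording. Restating the power needs no extra practices, and its cost is a less favourable stated figure. Keeping 90% as a two-sided target would be a different decision, needing about 13 practices per arm on the protocol's own assumptions. That choice is the sponsor's.

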**4. Study population**

We will include all registered patients within GP practices over the age of 70 years who do not currently have a diagnosis of dementia, live in a care home or have been referred to specialist memory services.

[figure not shown]

KEY

Problems experienced

Outcomes measured

[figure not shown]

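### The practice count divides a requirement in people with dementia by all patients referred, with no allowance for referrals not diagnosed with dementia

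*Protocol*

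**What the plan says.** Protocol, section 9, takes its standard deviation from people with dementia: "An audit of people with dementia presenting to Islington memory services showed a mean MMSE score =19.5 (standard deviation=6.1". The target difference is 3 MMSE points. The requirement is also counted in people with dementia: "To achieve this would require 71 undiagnosed people with dementia in each group". With an intracluster correlation of 0.03 (the digits 40 that follow it in the text are a reference number), this becomes 93 per arm.

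The conversion to practices uses a different unit. Islington had 420 patients referred from 38 practices in a year, a mean of 11, and then: "If 11 patients are referred per practice, we require approximately nine practices (clusters) in each trial arm". An attrition rate of 18%, attributed to illness, death and refusal of clinic assessment, raises nine practices to 11 per arm. Figure 2 carries this forward as 22 practices to randomise.

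Protocol, section 8, defines the primary outcome as the MMSE score of "people referred to memory services in the intervention and control groups who receive a diagnosis of dementia". Its secondary outcomes include "The number of people referred who do not have dementia or mild cognitive impairment", and costs are to cover assessment of people with and without dementia.

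**The concern.** The numerator (93) counts people with dementia; the divisor (11) counts people referred. A referral contributes to the primary analysis only if dementia is diagnosed. Someone found to have mild cognitive impairment, or neither condition, has no primary outcome. The protocol expects such referrals, since it plans to count and cost them, but section 9 makes no deduction for them. The 18% is already used up by the reasons given for it.

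At stake are the number of clusters and the 90% power. Section 10 relies on the sample size calculation to preserve power in a complete-case analysis. The number of practices is fixed at randomisation, so an analysis plan cannot repair it later.

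**Working it through.** **Inputs.** From protocol section 9: difference δ = 3, SD σ = 6.1, 5% significance, 90% power, ICC 0.03, 420 referrals from 38 practices, 18% attrition, 11 practices per arm. Not in the document: p, the share of assessed referrals who have the primary outcome, that is, who are diagnosed with dementia. I assume 50–90% for illustration.

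**Step 1: reproduce the plan.**
- n = 2(σ/δ)²(z₁₋α + z₁₋β)². One-sided: 2 × (6.1/3)² × (1.645 + 1.282)² = 70.8, so 71, as stated. Two-sided 5% would give 87. The plan's figure is therefore reproduced on a one-sided basis, which I use below.
- Design effect = 1 + (11 − 1) × 0.03 = 1.30. 71 × 1.30 = 92.3, so 93.
- 420/38 = 11.05. 93/11 = 8.45, so 9 practices.
- 9/0.82 = 10.98, so 11 practices.

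The chain reproduces in full, with each of the 11 referrals per practice treated as a dementia case.

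**Step 2: yield at 11 practices per arm.** 11 × 11 = 121 referrals. 121 × 0.82 = 99.2 assessed. Reaching 93 needs p = 93/99.2 = 93.7%.

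**Step 3: recompute the design effect.** The figure of 93 assumes 11 evaluable patients per practice. With fewer, the design effect falls and fewer than 93 are needed. Per practice, m = 11 × 0.82 × p = 9.02p. The design effect is DE = 1 + (m − 1) × 0.03, the yield is N = 11m, and the requirement is 71 × DE. Setting N equal to 71 × DE gives p of about 86%: m = 7.77, DE = 1.203, requirement 85.4, yield 85.4.

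**Step 4: power over the assumed range.** Power = Φ(δ/(σ√(2/(N/DE))) − 1.645).

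| Assumed p | m | DE | Yield per arm | One-sided power | Practices per arm for 90% |
|---|---|---|---|---|---|
| 90% | 8.12 | 1.214 | 89 | 91% | 11 |
| 80% | 7.22 | 1.186 | 79 | 88.5% | 12 |
| 70% | 6.31 | 1.159 | 69 | 85% | 14 |
| 60% | 5.41 | 1.132 | 60 | 81% | 15 |
| 50% | 4.51 | 1.105 | 50 | 75% | 18 |

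Worked line, p = 50%: N = 49.6, N/DE = 44.9, δ/SE = 3/(6.1 × √(2/44.9)) = 2.33, and Φ(2.33 − 1.645) = 0.753.

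The calculation assumes equal cluster sizes, equal arms, and an SD and ICC as stated.

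**The case against.** **The share is unknown, so no shortfall is shown.** This stands. A reader might infer that the trial cannot reach 93, or that power is lost by construction. The document does not support that: at a 90% share, 11 practices give 91% power on the plan's own basis. Between 86% and 94% the count falls below 93 while power stays at or above 90%.

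**The intervention should raise referrals.** This stands in part. More diagnoses and presentations are stated objectives in section 1, but any gain falls in the intervention arm only. As an illustration, 30% more evaluable patients in that arm gives one-sided power of 88% at a 70% share and 91% at 80%. With 50% more, it is 90% at a 70% share but only 81% at 50%. Section 9 claims no such gain.

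**Section 9 estimates 24 unknown cases per GP, which looks like a reserve.** This does not answer the point. The outcome exists only for those referred and diagnosed, and the practice count rests on 11 referrals.

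**Other stronger readings.** A reader might also infer that the 420 referrals include patients of any age or residence, set against a study population "over the age of 70 years who do not currently have a diagnosis of dementia, live in a care home". Section 9 does not describe the 420 further, so they may or may not have been restricted. Nor does the protocol state a cut-off that would exclude patients referred late in the 12 months.

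**Conclusion.** The unit mismatch is in the text, and section 9 is wrong as written: neither the nine practices nor the 11 derived from them allow for referrals not diagnosed with dementia, although section 8 expects them. The stated 90% power at 11 practices per arm needs about 86% of assessed referrals to be diagnosed with dementia (one-sided 5%, SD 6.1, ICC 0.03, 18% attrition, no extra intervention-arm referrals). Whether that share is met cannot be told from the protocol.

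The size of any loss rests on my assumed range. It runs from none at 90%, through 1.5 points at 80% and 5 points at 70%, to about 15 points at 50%. Confidence is high for the mismatch and low for its magnitude.

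Two-sided power would be lower, at 64–81% for shares of 50–80%. It would be wrong to charge that whole gap to this point, because two-sided power is only 87.5% even if every assessed referral has dementia. The sidedness of the test is a separate matter.

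**What to change.** In section 9:

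1. Replace 11 referrals per practice with the expected number of eligible, dementia-diagnosed referrals per practice. State the assumed share and its source: referral-level memory service data if available, otherwise a stated range. The audit cited for the MMSE mean and SD is described as covering people with dementia, so it cannot by itself supply the share of referrals who have dementia.
2. State whether the 420 Islington referrals were limited to the trial's eligible population (over 70, not in a care home, new referral). If not, allow for that as well.
3. Recompute the cluster size and design effect from that number.
4. Restate the expected evaluable number per arm and the power that 11 practices per arm deliver.

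The cost is a wording change and a short recalculation, plus a data request if referral-level data can be obtained. The downside is that the stated power may fall, or the number of practices may have to be reconsidered.

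### Practices are randomised within geographical strata, but the analysis section does not name the stratum; if location predicts MMSE, the cluster-adjusted test is mildly conservative.

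*Protocol*

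**What the plan says.** Section 9 of the protocol allocates whole GP practices, 11 per arm, and states: "Randomisation will be computerised and stratified by geographical location". It adds "The allocation ratio will be 1:1". The strata are neither defined nor counted.

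Section 10 describes the comparison of arms: a t-test or Mann-Whitney test of mean MMSE, a hierarchical regression, and analysis of covariance for baseline differences in outcome variables. On clustering it says "In the regression analysis we will account for the clustering effect in suitable ways (e.g. random effects models". On covariates it says "multiple linear regression will be used to identify other predictors of MMSE at presentation e.g. gender, age and ethnicity". The stratification factor appears in none of these sentences.

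Section 8 lists location among the sociodemographic items collected, so a term for it needs no new data. The same section says that MMSE is taken once, at presentation to the memory service, without follow-up scores.

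**The concern.** Stratified allocation balances location across the arms by design. Whatever MMSE differences exist between locations therefore largely cancel out of the difference between arms. A model with a practice random effect but no location term does not use this. It counts the variation between locations as variation between practices and carries it into the standard error. When location is prognostic, the reported interval is too wide and the test is conservative.

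What is at stake is precision, not validity: the estimate stays unbiased and the type I error falls below its nominal level rather than above it. The other adjustment in section 10 does not fill the gap. Analysis of covariance has no patient-level baseline MMSE to work with for the primary outcome, and the covariate list is there to find predictors of MMSE, not to define the comparison of arms.

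**Working it through.** **Inputs from section 9.** Audit data: "mean MMSE score =19.5 (standard deviation=6.1", so SD 6.1. Target: "A clinically significant difference between experimental and control arms =3 points in MMSE2", so 3 points (the final 2 is a reference number). Clustering: "we need to inflate the sample based on a projected intracluster correlation of 0.0340", so 0.03 (the final 40 is a reference number). Also 11 referrals per practice, 18% attrition and 11 practices per arm.

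**Reproducing the plan's figures.** "To achieve this would require 71 undiagnosed people with dementia in each group" is the start. One-sided 5%, 90% power: 2 × [6.1 × (1.645 + 1.282) / 3]² = 70.8, so 71, as stated. Two-sided 5% gives 86.9, so 87; the sidedness is a separate matter. Design effect 1 + (11 − 1) × 0.03 = 1.30; 71 × 1.30 = 92.3, so 93. Then 93 / 11 = 8.5, so 9 practices, and 9 / 0.82 = 10.98, so 11. The calculation takes no credit for stratification, so the planned size is unaffected.

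**Assumptions not in the protocol.** Let s be the share of between-practice variance that lies between locations; s = 0 to 0.75 is examined. Analysed patients per practice m = 11 × 0.82 = 9.02, so n = 11 × 9.02 = 99.2 per arm. Tests are two-sided at 5%. Four strata are assumed for the degrees of freedom: 22 − 2 = 20 without the stratum, 22 − 5 = 17 with it.

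**Formulas.**
- Variance factor reported without the stratum: V0 = 1 + (m − 1) × 0.03 = 1.2406.
- True variance factor under stratification: V1 = 0.97 + m × 0.03 × (1 − s).
- SE = 6.1 × √(2V / n).
- Overstatement ratio: r = √(V0 / V1).
- Type I error without the stratum: 2 × Φ(−1.96 r).
- Power without the stratum: Φ(3 / SE1 − 1.96 r). Power with it: Φ(3 / SE1 − 1.96). SE1 uses V1 in both, because the design is stratified whichever model is fitted.

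**At s = 0.5.** V1 = 0.97 + 9.02 × 0.03 × 0.5 = 1.1053; r = √(1.2406 / 1.1053) = 1.059; SE1 = 6.1 × √(2 × 1.1053 / 99.2) = 0.911. Power without: Φ(3.295 − 2.076) = 88.8%. Power with: Φ(3.295 − 1.960) = 90.9%.

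| s | r | Type I error without stratum | Power without → with (normal) | Power without → with (t, 20 → 17 df) |
|---|---|---|---|---|
| 0 | 1.000 | 5.0% | 87.5% → 87.5% | 84.1% → 83.4% |
| 0.25 | 1.028 | 4.4% | 88.2% → 89.2% | 84.7% → 85.4% |
| 0.5 | 1.059 | 3.8% | 88.8% → 90.9% | 85.3% → 87.4% |
| 0.75 | 1.093 | 3.2% | 89.6% → 92.5% | 86.0% → 89.3% |

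The t column uses the noncentral t distribution with the same SEs.

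**Simulation check.** Practice-level regression, 22 practices in four assumed strata (6, 6, 6 and 4), 9 patients each, 8,000 runs per setting. At s = 0.5, adding the stratum moved type I error from 4.0% to 4.8% and power from 85.8% to 87.8%. At s = 0, power went from 84.4% to 83.7%.

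**The t-test.** Its SE uses a variance factor of about 1, against a true V1 of 1.2406 at s = 0: a ratio of 1 / √1.2406 = 0.90 (0.88 with the full 11 patients per practice, 1 / √1.30). That is an understatement, in the opposite direction. It reverses only when V1 falls below 1, that is when 1 − s < 0.03 / 0.2706 = 0.11.

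**The case against.** The strongest reply is that exact model terms, stratification factors included, usually belong in the statistical analysis plan, which is not at hand. Section 10 gives its model and its covariates as examples, excludes nothing, and the protocol has location collected. A reader might infer that location is shut out of every analysis; an open list does not say that. This softens the point but does not remove it: section 10 does describe how the arms are compared and what is allowed for, and the factor that the design itself balances is absent.

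Three further inferences go beyond the documents.
- That standard errors will be overstated. This holds only if location predicts MMSE, and the sole MMSE figures given come from one audit in Islington. If location is unrelated, nothing is lost.
- That power at s = 0.5 rises from about 87% to 91%. This compares the adjusted analysis with a trial whose estimate really varies as V0 implies. Under stratification it varies less whichever model is fitted, so the fair comparison is 88.8% with 90.9%, about half that gain.
- That the strata are the memory services or trusts that measure MMSE. Section 9 does not define them, so this cannot be assumed.

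**Conclusion.** The point holds in a conditional and modest form. Section 9 stratifies by location, and the cluster-adjusted analysis in section 10 does not name the stratum. If location is prognostic, that model overstates its standard error: by 0 to 9% for an assumed share of 0 to 75% at the stated intracluster correlation of 0.03. At a share of 50%, the type I error is about 4%, and including the stratum gains about 2 points of power (88.8% to 90.9% with a normal reference, about 85% to 87% with a t reference). At a share of zero, inclusion costs under 1 point.

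The share, the four strata and the 9 analysed patients per practice are assumptions. The error is conservative, the estimate is unbiased and the sample size does not change. The conclusion does not extend to the listed t-test or Mann-Whitney. Severity is minor; this is a cheap improvement.

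**What to change.** Add one sentence to section 10: the cluster-adjusted models that compare arms will include, as a fixed effect, the geographical stratum actually used in randomisation. State in section 9 what the strata are, and keep them few, given 22 practices. The model should use those same strata, not a grouping chosen afterwards.

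The cost is one sentence and a few practice-level degrees of freedom (20 to 17 with four strata). No extra data or practices are needed. If location turns out not to matter, the loss is about 0.7 points of power.
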